## Method

The trial, registered as ISRCTN77313697, is a monocentric, two-arm, randomized, open-label study in cardiovascular patients to compare habit formation in a standard SPA-based CR program and a PAPA program.

### Sample size

The sample size was calculated using the simulation method of PASS 14 software (NCSS, Kaysville, USA) for power analysis with a mixed model. An alpha risk of 5 % and a bilateral hypothesis were taken into account for the power analysis. We estimated the expected scores of the participants in each arm of our study on the basis of the results of large-scale studies [34, 35, 38] that assessed PA behavior maintenance after CR with a questionnaire providing an average score of PA minutes per week. Given the linear effect of time, the change in PA behaviors after SPA suggested that the weekly time spent in PA behavior would be reduced by 5 min very month following the intervention. This result was used to infer the PA level of the group at each measurement point post-program. Several studies have shown that interventions designed to promote maintenance can lead to stabilized or even slightly increased PA behaviors over time (e.g., [2, 29, 34, 38]). We therefore predicted no change in the amount of PA behavior for the PAPA group after the intervention. The power analysis used a similar average score immediately after the intervention of 200 min/week for both groups, a general between-subject variability of 90 min/week, and an autocorrelation of the repeated measures of .55. ([name], [name], [name]. (unpublished manuscript). Testing the effect of text messaging cues to promote physical activity habits: A worksite-based exploratory intervention). The results after 1000 simulations indicated that 50 evaluable participants (25 participants in each arm) would be required to find the time-by-condition interaction effect with an 80 % power level. Assuming about 10 % of patients mistakenly included, lost to follow-up or withdrawing from the study, we randomized 56 participants (28 participants in each of the two arms).

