**Methods/Design:**

Cardiovascular patients (*N* = 56) will be individually randomized into two groups. Two supervised physical activity (SPA) sessions per week will be offered to the first group for 20 weeks. Progressively autonomous physical activity (PAPA) will be offered to the second group as follows: 10 weeks of the same supervised program as the SPA group followed by 10 more weeks in which one supervised session will be replaced by a strategy to build and sustain the habit of autonomous practice of physical activity. The primary outcome is the amount of physical activity measured by the International Physical Activity Questionnaire (IPAQ; Craig et al., Med Sci Sport Exercises 35(8):1381–95, 2003). To compensate for the limited capacity to recruit subjects, multiple IPAQ measurements will be made (at T0, T5, T7, T9 and T12 months after the start of the intervention) and analyzed using the mixed model approach. We will also assess changes in physical and physiological indicators, automaticity of the physical activity behavior, motivation and quality of life. Last, we will assess the cost-effectiveness for each type of program.

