## Discussion

Cardiovascular patients are generally willing to take part in CR, but unfortunately they do not systematically have the opportunity to do so (80 % of our sample). The PAPA intervention is designed to complement secondary prevention programs or replace them for those who cannot easily participate. The intervention aim is to provide cardiovascular patients with an opportunity to progressively learn, adopt and maintain PA behaviors.

The data from this study will be used to assess the impact of the *As du Coeur* intervention just after the end of the intervention (T5). We do not expect significant differences between the PAPA group and the fully supervised group at this point. Indeed, the fully supervised group will have more supervised sessions that the autonomous group (two per week versus one per week in the second half of the intervention). Based on the linear trend in the PA measures made in the months following the end of the intervention, we expect to find a decline in PA (negative linear slope of the time effect) post-intervention only for the SPA group. We expect that patients of the PAPA group will either maintain the same level (null slope) or even increase their PA (positive slope) in the months following the end of the intervention. Despite our low sample size due to a limited recruitment capacity, it is important to recall that this hypothesis can still be adequately tested with reasonable power using a mixed model approach, as simulation studies of the power in mixed model have shown that it typically increases with repeated measurements [23]. However, we will carry out exploratory analyses to test whether the PAPA intervention also leads to greater automaticity and motivation for PA, higher quality of life and better physical condition compared with the SPA intervention. Another limitation of the study can be the used of the sport motivation scale to assess participant’s motivation in the context of PA as motivation for sport and physical activity can differ.

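### The stated 80% power does not follow from the stated inputs: 25 per arm gives about 21% for the interaction test as written and about 32% for a linear-slope test

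*Protocol article*

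**What the plan says.** The Sample size section describes a simulation-based power analysis for a mixed model. On error rate it says "An alpha risk of 5 % and a bilateral hypothesis were taken into account for the power analysis". Both arms start at 200 min/week when the intervention ends. SPA then loses 5 min/week each month and PAPA does not change. The variance inputs are "a general between-subject variability of 90 min/week, and an autocorrelation of the repeated measures of .55". From 1000 simulations it concludes that "50 evaluable participants (25 participants in each arm) would be required to find the time-by-condition interaction effect" with 80% power.

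The Statistics and data analysis section fits time as a fixed factor at T5, T7, T9 and T12, with condition, their interaction, T0 IPAQ as a covariate and a random intercept per participant.

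Two other places rely on the power figure. The Abstract (Methods/Design) says "To compensate for the limited capacity to recruit subjects, multiple IPAQ measurements will be made", and the Discussion says "this hypothesis can still be adequately tested with reasonable power using a mixed model approach".

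**The concern.** The section prints both the inputs and the result, so the result can be checked. The hypothesised difference between arms is small against the variability: 35 min/week at the last visit, about 0.39 of the stated SD of 90 (35/90). A correlation of .55 leaves 45% of the variance within patients, and that part governs a time-by-condition test. With 25 patients per arm, 80% power looks out of reach.

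The figure matters because it is the stated justification for the sample size and for the Discussion's assurance about power. If true power is far lower, a non-significant interaction is the likeliest outcome even when the hypothesis is exactly right. A reader told that the trial was adequately powered could then take that outcome as evidence that PAPA does not help maintenance.

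**Working it through.** **Inputs**

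- Sample size section: both arms at 200 min/week at T5; SPA −5 min/week per month; PAPA flat; SD 90; correlation .55; two-sided 5%; 25 per arm.
- Statistics section: visits T5, T7, T9, T12, which are 0, 2, 4 and 7 months after the intervention; time as a four-level factor; random participant intercept, hence exchangeable correlation.

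Expected means are 200, 190, 180, 165 in SPA and 200 throughout in PAPA. The arm differences are 0, 10, 20 and 35 min/week.

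**The part that reproduces.** 50/(1 − 0.10) = 55.6, rounded up to 56. The dropout inflation is correct.

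**The plan's power figure, exchangeable correlation**

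1. Mean time = (0 + 2 + 4 + 7)/4 = 3.25 months. Sum of squared deviations: Sxx = 3.25² + 1.25² + 0.75² + 3.75² = 26.75.
2. Within-patient variance = 90² × (1 − 0.55) = 8100 × 0.45 = 3645.
3. Variance of one patient's slope = 3645/26.75 = 136.3.
4. SE of the slope difference = √(136.3 × 2/25) = 3.30.
5. Linear contrast (1 df): 5/3.30 = 1.51; power 32% (t, 48 df).
6. Interaction as written (3 df): the true difference is exactly linear, so noncentrality = (5/3.30)² ≈ 2.29; with 3 and 144 df, power 21%.

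A 20,000-replicate simulation gave 21.4% (3 df) and 32.8% (slope). At 80% power, 1000 simulations have a Monte Carlo standard error of √(0.8 × 0.2/1000) ≈ 1.3 percentage points, so simulation noise cannot explain the gap.

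**Other readings of 90 and .55, and other settings** (two-sided 5% and 25 per arm unless stated)

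| Reading | 3-df interaction | Linear slope |
|---|---|---|
| Exchangeable .55, total SD 90 | 21% | 32% |
| AR(1) .55 per visit | 12% | 18% |
| AR(1) .55 per month | 11% | 16% |
| 90 as random-intercept SD, ICC .55 | 13% | 20% |
| Exchangeable, all 28 per arm | 23% | 35% |
| Exchangeable, T0 added as fifth visit | 24% | 34% |
| Exchangeable, eight monthly visits | 22% | 46–47% |
| Exchangeable, alpha 10% | 32% | 44–45% |
| Exchangeable, 50 per arm | 40% | 56–57% |

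Where a range is shown, it reflects the choice of error degrees of freedom. A one-sided slope test gives about 44%. The T0 covariate does not help: it is constant within a patient and so leaves the within-patient variance unchanged.

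**What 80% would require** (exchangeable; each change alone)

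| Quantity | 3-df interaction | Linear slope |
|---|---|---|
| Evaluable per arm | about 120 | about 87 |
| Total SD at 25 per arm | about 41 | about 48 |
| Correlation at 25 per arm | about .91 | about .87 |
| Slope difference at 25 per arm (min/week per month) | about 11.1 | about 9.4 |

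**What the extra visits add.** With T5 and T12 only, Sxx = 3.5² + 3.5² = 24.5. Adding T7 and T9 raises it to 26.75. The slope variance ratio is 24.5/26.75 = 0.916, a reduction of about 8%. Power goes from about 29% for the T5-to-T12 change to about 32% for the four-visit slope.

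**The case against.** The strongest reply is that the covariance is not fully printed. Read literally, 90 is a between-subject component and .55 a serial correlation. The residual SD that drives the interaction would then be missing, and the simulation settings and the unpublished source of these inputs cannot be seen. With a random-intercept SD of 90 and independent residuals, 80% power is reached if the residual SD is about 27 (3 df) or 32 (slope). With AR(1) residuals at .55 it is about 29 or 33–34.

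That is arithmetically right but fits the text poorly. A residual SD of 27 implies a correlation between visits of 8100/(8100 + 27²) = .92, and 32 implies .90. The AR(1) version gives about .95–.96 between adjacent visits. The document gives .55 for the repeated measures. What stands is that no single replacement figure can be fixed until the covariance is stated, so 21% and 32% are conditional on the exchangeable reading. That is the most favourable of the covariance structures tried that keep both printed numbers.

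Second, the statement about compensating for limited recruitment is qualitative, and more visits do raise power. The direction is right and the gain is small: about three percentage points for the slope against the T5-to-T12 change. That does not make up for the shortfall in patients.

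Third, the article discloses its small sample and provides for 95% confidence intervals, and nothing in it says that non-significance will be read as no benefit. That is fair: the misreading is a risk, not something the plan announces. But the article also tells the reader that power is adequate, which invites it.

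**Conclusion.** The concern holds. The stated 80% is not reproduced by any reading tried that uses the printed inputs. At 25 per arm, power is about 21% for the time-by-condition interaction as specified and about 32% for the linear contrast that the Discussion describes. Serial-correlation and ICC readings are lower. The shortfall is 48 to 59 percentage points, or a factor of about 2.5 to 4. These figures assume complete data at all four visits, the stated means, a total SD of 90 and exchangeable correlation of .55. The settings behind the original simulation are not shown, so the source of the discrepancy is unknown.

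**What to change.** - **Sample size section:** state the covariance structure, say whether 90 is a total or a random-intercept SD, give the residual SD, and name the exact test simulated (3-df interaction or linear contrast). Rerun the simulation and replace 80% with the result. On the exchangeable reading this is about 21% or 32%. Equivalently, state that 50 evaluable patients detect a slope difference of about 9.4 min/week per month with 80% power on the linear contrast (about 11.1 on the 3-df test).
- **Discussion and Abstract:** remove the assurance of reasonable power and the statement that repeated IPAQ measurements compensate for limited recruitment. If a remark on repeated visits is kept, it should say that the gain is small here.
- **Interpretation:** state in advance that the estimated difference in change and its 95% confidence interval will carry the conclusion, and that a non-significant interaction will not be taken as evidence of no benefit.

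The cost is wording and one rerun of the simulation, plus a less favourable published figure. Recruitment, allocation and the analysis model are unaffected.

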### Participants

#### Recruitment strategy

The study is being conducted in the Alpes-Maritimes region of southern France; it began in 2014 and will run until 2016. CVD patients are identified from the electronic records of a public health insurance company for independent workers. The insurance company initially contacts the patients (*N* = 2248) by email, providing a detailed description of the project including the research objectives, subject requirements, timetable and the testing and training facilities. Potential participants are invited to contact the insurance company if they are interested in the experiment. Phone screening was conducted with 91 volunteers in October 2014. Then, they will have a free medical checkup with the study cardiologist, including a maximal effort test and an electrocardiogram.

#### Inclusion criteria

We restricted the study to adults over 18 years old, registered in the health insurance database with chronic disease (cardiovascular disease or cardiac deficiency) and considered as sedentary according to a brief physical activity assessment [27]. Further eligibility criteria include no contraindication to PA as certified by a cardiologist and ability to attend a 60-min session twice a week at a fitness center. The final sample will comprise 56 patients recruited on a voluntary basis.

### Consent

Consent to enter the study will be signed by each participant after they receive a full explanation in person, with the opportunity to ask questions. All participants have the right to decline participation or withdraw from the study at any time without giving a reason.

### Randomization

Randomization will be performed according to a 1:1 scheme, using the CS randomization Clinsight software module (Ennov, San Francisco, CA, USA). The method of randomization by minimization will be used to avoid imbalances between the two groups for all known and unknown patient-related factors that may influence the study outcome. Patient age (<65 years, ≥ 65 years), type of disease (coronary disease, cardiac insufficiency) and gender (Male, Female) will be stratified.

### Blinding

For practical reasons concerning the behavioral nature of the manipulation, strict participant blinding cannot be ensured. Several strategies will be implemented to prevent contamination and limit the potential biases associated with the lack of blinding [9].

In a randomized controlled trial in which the intervention is behavioral, hiding the content of the other study arm for participant blinding is difficult because true placebo conditions are unfeasible. To address this limitation, we adopted the double-consent procedure initially introduced by Zelen [47] and further adapted for behavioral intervention trials in patients with chronic disease [11]. In accordance with this procedure, eligible participants will first sign a general consent form and, after randomization, they will receive a second consent form detailing all the terms associated with their type of treatment without receiving any information about the study requirements concerning the other arm. It should be noted that a systematic review of the studies that have employed this procedure [1] indicated that this limited participant disappointment and increased the validity of the studies.

The investigators and PA coaches will be blinded to group assignment. The trial adheres to established procedures to maintain separation between the staff in charge of outcome measurements and the staff that will deliver the intervention. Staff members who obtain outcome measurements are not informed of the group assignment. In addition, those responsible for data analysis will be blinded to group status.

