### Intervention

The PAPA group will participate in two supervised sessions per week for the first 2.5 months and only one supervised session per week for the last 2.5 months. For the first 2.5 months, these patients will be advised to carry out at least one more session during the week on their own to meet the American College of Sports Medicine (ACSM) guidelines for cardiac patients [28]. However, they will be encouraged to carry out two autonomous sessions per week for the last 2.5 months. The supervised sessions will always be held at the same time of day and on the same day of the week with the same instructor. These sessions will include one session of Nordic walking (45 min to 1 h) at low to moderate intensity and one session of circuit training (1 h) at moderate to high intensity. The intensity levels will be defined in accordance with ACSM guidelines [28]. The session contents will be individualized according to each patient’s heart rate using a heart rate monitor (Polar FT1 heart-rate monitor watch). After controlling the resting heart rate and maximal heart rate, training windows will be calculated for each participant and used during the PA sessions. This will allow them to work at different intensities. The instructor will be trained to deliver an autonomy-supportive coaching style [41] as autonomous motivation has been shown to strengthen habit formation [19]. The tools we will use and the strategies we will implement are all aimed at supporting exercise instigation in terms of planning and preparatory behaviors (Barz et al. [4]). The goal is to develop autonomy, self-confidence and knowledge so that the participants can exercise by themselves in their homes. An individualized exercise prescription based on heart rate and current exercise capacity will be a core component of the intervention. Autonomous practice will be promoted in this group with support to aid habit formation. First, they will receive a pamphlet on PA (i.e., tips on safety rules, health benefits, nutrition, stretching, how to use a heart rate monitor, how to breathe) and a PA program containing a list of Nordic walking and cardio-training activities that can be done in their home environment. They will also receive the calendar used by Gardner et al. [20] that can be used as a tool for forming new habits. The calendar is generic and patients will be invited to use it in planning when and where they will do their PA sessions; they will thus be expected to write session plans down on the calendar. They will be advised to put the calendar in a place where they will see it every day (e.g., on the fridge and/or a bathroom mirror) so that they will have frequent reminders of their PA session. They will then be called every 2 weeks for an approximately15-min conversation with a researcher trained in habit formation theory. This researcher will help the patients to choose an appropriate moment and an appropriate context for the autonomous PA sessions and remind them to stick with their plans.

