#### Behavioral measures

PA behavior will be assessed using a self-report questionnaire extensively used in the literature, the International Physical Activity Questionnaire (IPAQ) [14] at time (T) 0, T5, T7, T9 and T12 months. The questionnaire responses will be computed as energy requirements defined as METs (multiples of the resting metabolic rate). Based on previous research in other chronic diseases (e.g., [31, 32]), a subsample using a GT3X+ accelerometer will comprise 30 % of the participants selected randomly from among volunteers. According to this meta-analysis, an acceptable level of agreement between IPAQ and GT3X+ indicated a small to moderate association (r = .29). They will wear the GT3X for one week (score in METs) at T0, T5 and T12 in order to check whether the self-reported PA measure correlates with the objective PA measure in the context of our study. The PA adherence will be assessed by reporting on the participation in the two supervised sessions per week and the autonomous session.

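### The Blinding section says coaches and investigators are blinded, which the intervention rules out for coaches; the accelerometer correlation is almost insensitive to over-reporting that differs between arms

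*Protocol article*

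**What the plan says.** **Who is blinded.** The Method section says the trial "is a monocentric, two-arm, randomized, open-label study in cardiovascular patients". The Blinding section concedes that "strict participant blinding cannot be ensured" and describes a double-consent procedure in which patients sign a second, arm-specific form "without receiving any information about the study requirements concerning the other arm". It then states: "The investigators and PA coaches will be blinded to group assignment". It adds that outcome staff are separate from delivery staff ("Staff members who obtain outcome measurements are not informed of the group assignment") and that analysts are blinded.

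**What is delivered.** According to the Abstract and the Intervention section, both arms have two supervised sessions a week for the first 10 weeks. PAPA then drops to one a week for the remaining 10 weeks, while SPA keeps two. Supervised sessions are at fixed times with an unchanging instructor. PAPA patients also receive a habit calendar, and "They will then be called every 2 weeks for an approximately15-min conversation with a researcher trained in habit formation theory". Neither is described for SPA.

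**Outcome and check.** The primary outcome is the self-reported IPAQ at T0, T5, T7, T9 and T12. Under Behavioral measures, an accelerometer is worn at T0, T5 and T12 by 30% "of the participants selected randomly from among volunteers". Its stated purpose is to see whether the two measures correlate. With reference to a cited meta-analysis, the section gives a benchmark: "an acceptable level of agreement between IPAQ and GT3X+ indicated a small to moderate association (r = .29").

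**The concern.** Two separate things are at stake.

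First, the article claims a safeguard that its own Intervention section rules out for at least the coaches and the calling researcher. A reader judging risk of bias would credit the trial with blinded delivery that it does not have.

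Second, the safeguards that can work (uninformed outcome staff, blinded analysts) act on the collection and handling of data. With a self-report questionnaire the patient is in effect the assessor, and patients know their own programme. As described, only PAPA patients are phoned by a researcher who helps them plan sessions and reminds them to keep to those plans. That is a plausible route to reporting error that differs by arm, although nothing in the article shows that it will occur. The accelerometer is the only planned measure of activity amount that does not rely on self-report, and its stated use is a correlation, which is poorly suited to showing such a difference.

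**Working it through.** **1. Blinding, passages side by side.** Open-label (Method) against blinded coaches (Blinding). With a fixed timetable and an unchanging instructor (Intervention), the instructor sees which patients give up one of their two weekly sessions at the halfway point. The researcher making the habit calls knows the arm because the calls are described for PAPA only. The term investigators is not defined, so for other investigators the claim is neither shown nor excluded.

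**2. Size of the subsample.** Sample size section: 50 evaluable with about 10% loss, 50/(1 − 0.10) = 55.6, rounded up to 56. The plan's figure reproduces. Then 0.30 × 56 = 16.8, about 17, or 8 and 9 per arm if balanced.

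**3. Precision of a correlation at the benchmark value.** Fisher z with r = .29 and n = 17:
- z = atanh(.29) = .2986; SE = 1/√14 = .267
- 95% limits on the z scale: .2986 ± 1.96 × .267; back-transformed, −.22 to .68
- Two-sided 5% power against zero: about 20%
- n for 80% power: ((1.96 + .8416)/.2986)² + 3 = 91.05, so 92
- With 15 patients (30% of 50): −.26 to .70, power about 18%

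**4. Response of the pooled correlation to over-reporting in one arm.** The Sample size section assumes SPA falls by 5 min/week each month and PAPA does not change, so the T12 difference is 5 × 7 = 35 min/week, with SD 90. If a fraction p of patients over-reports by δ and true activity is the same in both arms, the correlation becomes r/√(1 + p(1 − p)(δ/90)²). With p = 9/17, p(1 − p) = .249:
- δ = 35: .29/√(1 + .249 × .151) = .29/1.019 = .285
- δ = 70: .29/√(1 + .249 × .605) = .29/1.073 = .270

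In 20,000 simulated samples of 17 the mean correlation was .28, .28 and .26 for δ = 0, 35 and 70, with a sampling SD of .23 each time. The correlation does fall, but by far less than its sampling noise.

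**5. What would bias the primary test.** Under Statistics and data analysis, the test is the arm-by-time interaction over T5, T7, T9 and T12. Let PAPA over-report relative to SPA by b5 at T5 and b12 at T12. The contrast (PAPA T12 − PAPA T5) − (SPA T12 − SPA T5) is then biased by b12 − b5. A constant over-report gives b12 − b5 = 0. A false PAPA benefit needs b12 > b5, and bias alone would reproduce the whole assumed effect at b12 − b5 = 35 min/week. If over-reporting faded once the programme ended, b12 < b5 and the bias would run against PAPA.

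**6. What a by-arm comparison could show.** The SD of the IPAQ-minus-accelerometer difference is not in the document; a range of 60–120 min/week is assumed. For 8 against 9 patients, SE = SD × √(1/8 + 1/9) = SD × .486.

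| Assumed SD | SE | 95% half-width | Power for 35 | Detectable at 80% power |
|---|---|---|---|---|
| 60 | 29.2 | 57 | 22% | 82 |
| 90 | 43.7 | 86 | 12% | 122 |
| 120 | 58.3 | 114 | 9% | 163 |

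For the T5-to-T12 change in the discrepancy, the relevant SD is SD × √(2(1 − ρ)), where ρ is its within-patient correlation. It equals the single-visit SD when ρ = .5 and is larger when ρ is lower.

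**The case against.** The strongest reply is that only the sentence on coaches is wrong, that this is a one-line correction, and that the rest either misses the primary test or belongs in the analysis plan. Much of this stands:

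- A constant over-report does cancel from the planned interaction. The calls are described within the intervention and nothing says they continue to T12, so the direction of any bias is open.
- Real safeguards exist: separate and uninformed outcome staff, blinded analysts, and double consent that withholds the other arm's content. The article also admits openly that patients are not strictly blinded.
- The value .29 comes from the literature. No rule is set by which the check passes or fails.
- The 6-minute walk, handgrip and sit-to-stand tests at T0, T5 and T12 do not depend on self-report and can be compared by arm. They measure physical condition, though, not amount of activity.
- The article may leave accelerometer details to a fuller document. What it does state, however, is the purpose of the device, and that purpose is a correlation.

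A reader might infer that a PAPA advantage could be pure reporting bias that the check would wave through, or that no blinding safeguard exists. The document supports neither. The first would need a reporting difference that grows after T5, for which there is no evidence, and there is no pass mark. The second overlooks the outcome staff and the analysts.

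What the reply does not remove is that the blinding statement conflicts with the design, and that a pooled correlation does not address reporting error that changes differently in the two arms.

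**Conclusion.** The point holds in limited form. Blinding of coaches, and of the researcher who phones PAPA patients, cannot be squared with the Method and Intervention sections; the status of other investigators is undefined. Blinding of outcome staff and analysts is feasible and is not in question.

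The planned accelerometer check is nearly insensitive to arm-dependent over-reporting: a 35 min/week shift in one arm moves the expected correlation by less than .01, against a sampling SD of .23. This rests on about 17 patients, an SD of 90, a true correlation of .29 and equal true activity in the two arms. For the primary analysis the relevant threat is a between-arm difference in reporting error that changes between T5 and T12. The document neither shows that this will occur nor plans a check aimed at it. The wording should be corrected, and the data already planned should be put to better use; the point does not invalidate the primary analysis.

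**What to change.** 1. Rewrite the blinding paragraph. State that outcome-collection staff and analysts are blinded; that coaches, the calling researcher and patients (who know their own programme) are not; and which investigators, if any, are. Keep the open-label label consistent with this.
2. Draw the accelerometer subsample evenly by arm, about 8 to 9 each.
3. Keep the correlation, and add by arm the IPAQ-minus-accelerometer difference in the same units at T0, T5 and T12, its T5-to-T12 change, and the PAPA-minus-SPA difference in that change with a 95% CI. Report the accelerometer PAPA-minus-SPA contrast as well.
4. Say in advance that these are descriptive supporting estimates. They should not veto the primary result, because 8 to 9 patients per arm would often contradict a true effect by chance; nor should a non-significant discrepancy be read as reassurance.

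Cost: wording, one constraint on the subsample draw, and a short additional table. No extra devices, visits or staff are needed. The drawback is imprecision, with the half-widths and power shown in the table above, and the results will apply only to patients who volunteered to wear the device.
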